### Blinding

The statistician involved in the data analyses will be blinded to the intervention allocation.

### Analysis

The primary outcome, health care expenditures, will be calculated in two parts. First, a chi-square test will be used to do a crude comparison of the attendance rates of the two groups (intervention and control). Second, health care costs differences will be measured and tested using difference-in-difference analysis. The secondary outcome, societal costs, will also consist of two parts. First, the effect; a marker of reduced alcohol consumption after 12 months (i.e. alcohol related health care contacts), will be assessed in a difference-in-difference analysis. Second, the societal costs will be analysed like health care costs. Cost data are non-Gaussian and non-linear statistical models and bootstrapping techniques will be used in the statistical analyses.

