**Method/Design:**

The study is a single-blind pragmatic randomized controlled trial including patients admitted to the hospital. The study group (*n* = 500) will receive an intervention, and the control group (*n* = 500) will be referred to treatment by usual procedures. All patients complete a lifestyle questionnaire with the Alcohol Use Disorders Identification Test embedded as a case identification strategy. The primary outcome of the study will be health care expenditures 12 months after discharge. The secondary outcome will be the percentage of the target group, who 30 days after discharge, reports at the alcohol treatment clinics. In order to analyse both outcomes, difference-in-difference models will be used.

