### Inclusion and randomization

The procedure for inclusion and randomization of the patients is shown in the flow chart (Fig. 1 in Appendix). As a part of standard procedures and quality management, all consecutive patients in the participating departments will be asked to complete a 27-item lifestyle assessment questionnaire concerning smoking, nutrition, exercise and alcohol. The questions on alcohol will include the ten questions in the Alcohol Use Disorders Identification Test. The staff hands out the questionnaire to all patients admitted to the participating departments. Hereafter, the staff collects and scores the questionnaires according to the recommendations [12]. The staff reports the scores to the alcohol treatment clinic, daily. According to randomization, the patient will be allocated to intervention group if the patient meets the following inclusions criteria:Not participated in any alcohol-specific treatment for alcohol use disorders in the previous 6 monthsNot psychoticMore than 18 years of ageHospitalized for a minimum of 24 hResident within the uptake area of the involved alcohol treatment clinicsWilling to participate in the studyCognitively and physically capable.

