## Outcomes

### Primary outcome

Health care expenditures 12 months after discharge.

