### Power calculation

In the absence of data from general hospitals, we use data for the power calculation stemming from the study by Parthasarathy et al., who found that outpatient treatment decreased the consumption of health services by 26 % [29]. Primary outcome is the socio-economic costs of alcohol-abuse patients. Based on information from the Danish Institute of Governmental Research we have an estimate of the average total additional expenses for alcohol abuse patients of 88,067 DKK. Treatment for alcohol dependence is expected to lower the additional costs by 26 %. Since the individual excess costs of patients is highly variable with a standard variation of 144,967 DKK, the coefficient of the variation is quite high. Therefore, the power calculation results in a total of about 500 patients in each of the two groups in order to be able to detect the average decrease in total additional expenses of 22,897 DKK, with 80 % probability.

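### The primary cost test is a difference-in-difference, but the trial was sized on the SD of cost levels, so the stated 80% power does not describe it; adjusting for pre-period cost is at least as efficient

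*Protocol article*

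**What the plan says.** All references are to the protocol article.

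- **Primary outcome section:** the outcome is a level, "Health care expenditures 12 months after discharge".
- **Analysis section:** for the primary outcome, "health care costs differences will be measured and tested using difference-in-difference analysis". Non-linear models and bootstrapping are also named, with no link function.
- **Power calculation section:** the inputs are "average total additional expenses for alcohol abuse patients of 88,067 DKK", a 26% reduction, and the statement that "individual excess costs of patients is highly variable with a standard variation of 144,967 DKK". The result is about 500 per group to "detect the average decrease in total additional expenses of 22,897 DKK, with 80 % probability". No alpha, sidedness, SD of change or correlation between prior and follow-up cost is stated.
- **Abstract, Method/Design:** after naming 12-month expenditures and 30-day attendance at the clinics, it says "In order to analyse both outcomes, difference-in-difference models will be used".
- **Analysis section, attendance:** a crude chi-square comparison of the two groups, listed as the first part of the primary outcome analysis.
- **Inclusion and randomization section:** patients must not have had "any alcohol-specific treatment for alcohol use disorders in the previous 6" months.
- **Follow-up data section:** registry data are collected 12 and 60 months after discharge. The article does not define the pre-period that a difference-in-difference on costs needs.

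**The concern.** A difference-in-difference compares mean changes between arms. Its precision depends on the SD of the change, and so on how strongly prior and follow-up costs correlate. The sample size uses the SD of a level. The two agree only by coincidence, so the reader does not know what power the primary test has.

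There is also a question of efficiency. When arms are randomised, subtracting the whole of the baseline value adds noise if the correlation is weak, whereas regressing on baseline removes only as much as the correlation justifies. The planned method may therefore give up power on the primary outcome when the same data would support a more precise analysis.

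For attendance, the article names two different methods, and one of them has nothing to difference.

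**Working it through.** **Inputs.** Δ = 22,897 DKK (0.26 × 88,067 = 22,897.4), SD σ = 144,967 DKK, 500 per group and 80% power, all from the Power calculation section. Not given, so assumed: alpha and sidedness, r, and the ratio k of pre-period SD to follow-up SD.

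**Step 1: reproduce the 500.** n per group = 2(z_α + z_β)²(σ/Δ)², with (144,967/22,897)² = 40.09.

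- One-sided 5%: 2 × (1.645 + 0.842)² × 40.09 gives 496. Power at 500 is 80.3%.
- Two-sided 5%: 2 × (1.960 + 0.842)² × 40.09 gives 630. Power at 500 is 70.4%.

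The stated figure matches an unadjusted comparison of levels at one-sided 5% (equivalently two-sided 10%). I use that setting below, so that the effect of the estimator is not mixed with the separate question of sidedness.

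**Step 2: variance of each estimator**, relative to follow-up only (factor 1), linear model, large sample:

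- Difference-in-difference: 1 + k² − 2kr, which is 2(1 − r) when k = 1.
- Adjustment for pre-period cost: 1 − r².
- Gap: (1 + k² − 2kr) − (1 − r²) = (k − r)², never negative and zero only at r = k.
- Difference-in-difference beats follow-up only when r > k/2, that is r > 0.5 when k = 1.

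**Step 3: power at 500 per group.** Power = Φ(Δ / (σ√(2f/500)) − 1.645), where f is the variance factor. For f = 1, Δ divided by its standard error is 22,897/9,169 = 2.497. With k = 1:

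| r | DiD factor | DiD power | DiD n for 80% | Adjusted factor | Adjusted power | Adjusted n for 80% |
|---|---|---|---|---|---|---|
| 0 | 2.00 | 54.8% | 992 | 1.00 | 80.3% | 496 |
| 0.2 | 1.60 | 62.9% | 794 | 0.96 | 81.7% | 476 |
| 0.3 | 1.40 | 67.9% | 694 | 0.91 | 83.5% | 452 |
| 0.4 | 1.20 | 73.7% | 595 | 0.84 | 86.0% | 417 |
| 0.5 | 1.00 | 80.3% | 496 | 0.75 | 89.2% | 372 |
| 0.6 | 0.80 | 87.4% | 397 | 0.64 | 93.0% | 318 |
| 0.7 | 0.60 | 94.3% | 298 | 0.51 | 96.8% | 253 |

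At two-sided 5% the ordering is the same: 56.0% against 74.5% at r = 0.3, 70.4% against 82.2% at r = 0.5, and 89.7% against 93.8% at r = 0.7. In that setting the follow-up-only analysis already has just 70.4%, so not all of the shortfall from 80% comes from the estimator.

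**Step 4: unequal SDs.** At r = 0.3 the adjusted factor is 0.91 whatever k is. The difference-in-difference factor is 0.95 at k = 0.5, 1.07 at k = 0.7, 1.40 at k = 1 and 1.91 at k = 1.3. The gap can almost vanish or grow well beyond the table.

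**Step 5: attendance.** Eligibility sets prior attendance to zero in both arms over the previous 6 months. The difference-in-difference is then (p₁ − 0) − (p₀ − 0) = p₁ − p₀, the plain difference in proportions that a chi-square test addresses.

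**The case against.** A reader might infer that difference-in-difference is simply the wrong estimator here. The documents do not support that. Under randomisation it is unbiased for the mean cost difference, and with equal SDs and r above 0.5 it is more powerful than the analysis the trial was sized on. The issue is efficiency and the mismatch with the sample size.

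There is a real argument for it in this design. Days are randomised, and on intervention days patients are informed and asked for consent before receiving the intervention, while controls get usual procedures. If this leaves the arms systematically different at baseline, difference-in-difference removes stable between-group differences that regression on baseline may not. The article does not give this as its reason, but the point stands and is why the method should stay as a sensitivity analysis.

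The percentages are also conditional. The SD is a cost-level SD from an outside source for total additional expenses. It is not labelled as the follow-up SD of 12-month health care expenditure. The formulas are for linear models and ignore any clustering by day.

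Two other inferences go too far. One is that difference-in-difference cannot work for attendance: it collapses to the simple difference, and the Analysis section already plans a suitable between-group test. The other is that the non-linear models make the effect a ratio of ratios: that would need a log link and an interaction coefficient as the estimand, and the article names neither.

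Choice of covariates is ordinarily left to a full analysis plan. The conflict between the stated test and the stated power is not, because both are in the article.

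**Conclusion.** The point holds as a mismatch and an avoidable inefficiency. The stated 80% power belongs to an unadjusted comparison of cost levels at one-sided 5%, whereas the planned primary test is a difference-in-difference whose power depends on an unstated r. With equal pre and post SDs, the planned test falls short of the stated power only if r is below 0.5, for example 67.9% at r = 0.3. Adjustment for the same pre-period cost is never less efficient in a large-sample linear model. Over r from 0.2 to 0.7 it gains between 18.8 percentage points (81.7 − 62.9) and 2.5 points (96.8 − 94.3) over difference-in-difference. The gain depends on the ratio of pre to post SD and disappears when that ratio equals r.

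The documents do not show that the trial is underpowered because of this choice, since r is unknown. For attendance, the defect is a conflict of wording between the abstract and the Analysis section, with little practical consequence.

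**What to change.** 1. Make the primary cost model 12-month post-discharge cost by arm, adjusted for cost in a named pre-period (the one difference-in-difference needs in any case), AUDIT score and the recorded demographics. Report the mean difference in DKK with bootstrap intervals, whatever link is used.
2. Keep difference-in-difference as a sensitivity analysis, stating that it rests on different assumptions if the arms are unbalanced at baseline.
3. State in the Power calculation section that the figure refers to an unadjusted comparison of levels, with its alpha and sidedness.
4. Limit the abstract's difference-in-difference sentence to costs and, in line with the Analysis section, alcohol-related contacts. Name one between-group comparison of proportions for 30-day attendance.

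The cost is a change of wording made before unblinded analysis. It needs no extra patients and no data beyond what difference-in-difference already requires. The small downside is that the primary result would rely more on randomisation having balanced the arms; the sensitivity analysis covers this.

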### Ethics

All participating patients with a score of 8+ in the Alcohol Use Disorders Test, suggesting an alcohol use disorder, will be addressed. All data collected in the study will be treated strictly confidentially. No analysis or publication will contain information that allows person-identification. As the study will be based on registers, thus as it does not include human biological material, the study does not need approval from the Regional Scientific Ethical Committees of Southern Denmark [42]. The study was approved by the Danish Data Protection Agency. The study applies to the declaration of Helsinki [43].

### Recruitment

Recruitment started on November 1^st^ 2013. According to the power calculation and based in statistics on admittances, the inclusion will end in the summer of 2016. Follow-up will finish in 2020.

## Discussion

Economic costs are important endpoints in this study. Our economic data and analyses really address several related objectives. Firstly, we believe that economic costs serve as valid indicators of the health and social impacts of our intervention. If the intervention is successful it should show in lower health care expenditures and, in particular, in reduced social costs. In a Danish setting, with an integrated public health sector with basically one third-party payer (the Government) and likewise for delivery of social and welfare services, and with our population registries, we are able to achieve reliable cost data. Secondly, the estimation of economic impacts of our intervention is important in order to politically motivate its implementation and to sort out the financial implications for various public budgets involved.
